#### Clinical measures – Secondary

Secondary outcomes will evaluate: (1) mental health problems commonly experienced by people with psychosis (anxiety and depression (Hospital Anxiety and Depression Scale) [38] and paranoia (Paranoid Thoughts Scale) [39]); (2) variables that have been associated with the impact of voice-hearing (negative beliefs about the self (Self Scale of the Brief Core Schema Scale) [40], negative beliefs about voices (Beliefs About Voices Questionnaire – Revised) [41] and negative relating to voices (Voice and You) [42] and other people (Persons Relating to Others Questionnaire) [43]; and (3) a range of personal and social recovery-oriented outcomes (goals for the outcome of CBTp (CHOICE – short form) [44], the positive impact of voices (Voice Impact Scale) [45], engagement in meaningful activity (Work and Social Adjustment Scale) [46] and social functioning (Social and Occupational Functioning Scale) [47].

#### Process measures

Process measures will evaluate the quality of the therapeutic relationships (Scale to Assess Therapeutic Relationships) [48] and participants’ expectations for therapy (Therapy Credibility and Expectancy Questionnaire) [49].

#### Health economic measures

The *EuroQol 5 dimensions, 5 levels health survey (EQ-5D-5 L)* [50] *–* is a standardised instrument used as a measure of health-related quality of life that can be used in a wide range of health conditions and treatments. The descriptive system comprises five dimensions: mobility, self-care, usual activities, pain/discomfort and anxiety/depression. Each dimension has five levels: no problems, slight problems, moderate problems, severe problems and extreme problems.

The *Client Service Receipt Inventory (CSRI-UK)* [31] *–* is a well-validated adaptable research instrument used in mental health settings to collect information on health, social and voluntary service utilisation, informal care, accommodation, other public services (e.g. police) and private out-of-pocket expenses incurred. Its primary purpose is to allow resource-use patterns to be described and costs to be estimated.

The *Short Form 12 (SF-12)* [51] *–* this generic health survey captures information about functional health and well-being from the patient’s point of view.

### Plans to promote participant retention and complete follow-up {18b}

Efforts will be made to engage all participants in follow-up assessments. RAs will flexibly engage patients, offering appointments at times and locations which best suit participants and offering shorter and split assessment sessions as needed. Participants will be offered reimbursement of £20 per assessment point (i.e. baseline, 16 and 28 weeks) and travel expenses will be made available. Retention rates will be monitored by the trial manager at least weekly and the research team on a monthly basis throughout the trial. The Lived Experience Advisory Panel (LEAP) will be asked to provide consultation regarding retention rates as part of their oversight role.

### Data management {19}

Data collection and analysis will be supervised by the Trial Statistician. The management of the data will be a standing item on the agenda of the monthly meeting of the research team. All members of the research team and any other individuals from collaborating Trusts or Universities involved in collecting, inputting, processing, using and sharing data will have had Information Governance training.

### Confidentiality {27}

The minimum amount of personal information needed to conduct the study will be obtained from participants. Personal and research data will be stored securely on NHS premises. Physical data, such as consent forms, will be locked in filing cabinets on NHS premises accessible only to members of the research team. Electronic data will be stored securely in password-protected or encrypted files on NHS computers accessible only to members of the research team. All research data will be fully anonymised and will be stored separately to personal data. A link file will allow for participant research data to be identified. This link file will be a password-protected file accessible only by members of the trial team within each research site and the trial manager. This file will be securely destroyed following the end of the study. Quantitative and qualitative data will be appropriately aggregated in any publications arising from the trial to protect participant anonymity during and after the trial has ended.

## Statistical methods

### Statistical methods for primary and secondary outcomes {20a}

Analyses will be based on the intention-to-treat approach. All clinical outcomes will be summarised using descriptive statistics at pre-randomisation (T0), at 16 weeks (T1) and at 28 weeks (T2) for each arm (GiVE, SC and TAU) of the study. Next, 95 and 75% confidence intervals [51] will be created for between-group mean differences after adjustment for the baseline scores using analysis of covariance (ANCOVA) for the following comparisons: GiVE vs TAU; GiVE vs SC; and TAU vs SC. There will be no hypothesis testing.

Analysis will be conducted using a linear mixed model with a random effect for individual with fixed effects for treatment group (TAU, GiVE and SC) and time (16 and 28 weeks); baseline score and site will be entered as covariates. Contrasts will be used to compare groups (GiVE vs TAU, GiVE vs SC and TAU vs SC) at T1 and T2. 95 and 75% confidence intervals [25] for between-group mean differences will be created for all estimates of unstandardised effect size.

Standardised (Cohen’s *d*) effect sizes for each outcome will be calculated by dividing the between-group unstandardised effect by the baseline pooled standard deviation. The level of missing data will be summarised for each outcome and reported for each time point.

Two potential primary outcomes – the Distress scale of PSYRATS and the Negative Impact scale of the HPSVQ – are being explored in this feasibility study. In addition to the analyses for all clinical outcomes, the between-groups differences for these two variables will be assessed in the context of:
Whether the minimal clinically important difference (MCID) is contained within the 95% confidence intervals where:
◦ PSYRATS Distress scale of MCID is a 3-point reduction◦ HPSVQ Negative Impact scale MCID is a 2-point reductionThe level of missing dataPopularity of the outcome in the literatureAny other relevant information generated by the process evaluation

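### Two models are set for the same three contrasts with no source named for Cohen's d or the MCID check, and the mixed model as listed cannot separate T1 from T2

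*Protocol article*

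**What the plan says.** All of this is in the protocol article, Statistical methods for primary and secondary outcomes {20a}, unless another section is named.

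- First paragraph: "95 and 75% confidence intervals [51] will be created for between-group mean differences", obtained "after adjustment for the baseline scores using analysis of covariance (ANCOVA) for the following comparisons": GiVE against TAU, GiVE against SC, and TAU against SC. Baseline score is the only covariate named, and no time point is attached to the ANCOVA.
- Second paragraph: "Analysis will be conducted using a linear mixed model with a random effect for individual with fixed effects for treatment group" and time (16 and 28 weeks), where "baseline score and site will be entered as covariates". It continues: "Contrasts will be used to compare groups (GiVE vs TAU, GiVE vs SC and TAU vs SC) at T1 and T2". Intervals at 95% and 75% are requested again.
- Third paragraph: Cohen's d is the unstandardised between-group effect over the pooled baseline SD. The model supplying that effect is not named.
- Last paragraph: the two candidate primary outcomes are judged partly on whether the MCID (3 points for PSYRATS Distress, 2 points for HPSVQ Negative Impact) lies inside the 95% interval. Again no model is named. Three other considerations follow: missing data, popularity in the literature, and information from the process evaluation.
- Sequence generation {16a}: randomisation is stratified by site and by type of service.

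**The concern.** Two models with different covariates and structure are each told to deliver the same intervals for the same comparisons, and neither is called main or supporting. Where they differ, two values exist for one quantity, and the text does not settle which one enters Cohen's d or the MCID check. Both feed the planning of the definitive trial.

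The second model has its own difficulty. Its listed fixed effects force the arm difference to be equal at the two follow-up visits, yet the next sentence promises a comparison at each visit. Its covariates include one stratification factor and not the other.

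**Working it through.** **Inputs from the protocol.** 90 patients (Sample size {14}) at 1:1:1, so 90/3 = 30 per arm. Three contrasts, two follow-up times, HPSVQ Negative Impact MCID of 2 points. The plan gives no figure for this point to reproduce.

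**Step 1: the two descriptions side by side.**

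| | ANCOVA paragraph | Mixed-model paragraph |
|---|---|---|
| Contrasts | GiVE–TAU, GiVE–SC, TAU–SC | the same three |
| Intervals | 95% and 75% | 95% and 75% |
| Covariates | baseline | baseline, site |
| Time | none stated | 16 and 28 weeks |
| Random effect | none | individual |
| Named as source for d or MCID check | no | no |

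**Step 2: what the mixed model as listed can estimate.** Write the mean for patient i at visit t as

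μ = a + b·GiVE + c·SC + e·[t = T2] + f·baseline + h·site.

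For the same baseline and site, GiVE minus TAU at T1 is (a + b) − a = b. At T2 it is (a + b + e) − (a + e) = b. The time effect cancels, so the contrasts at T1 and T2 are one and the same number. Separate contrasts need terms GiVE×T2 and SC×T2.

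**Step 3: how far the models differ.** GiVE vs TAU was simulated with 30 per arm and 400 runs per scenario. Assumptions not in the protocol: normal scores with SD 3.5; correlation 0.5 between baseline and each follow-up and 0.6 between T1 and T2; no missed visits, or 15% missed at T1 and 20% at T2, independently at random; true reductions of 0.5 or 2 points. The ANCOVA was fitted at each visit with baseline. The mixed model had baseline and site (site without a true effect). Each cell gives T1 / T2. 'Gap' is the mean absolute difference between the two estimates in points. 'MCID' is the share of runs in which the models disagree on whether a 2-point reduction lies inside the 95% interval.

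| True effect | Missed | As listed: gap | As listed: MCID | With group-by-time: gap | With group-by-time: MCID |
|---|---|---|---|---|---|
| 2 / 2 | none | 0.33 / 0.33 | 4.8% / 4.0% | 0.06 / 0.06 | 1.5% / 2.2% |
| 2 / 2 | 15% / 20% | 0.39 / 0.43 | 6.5% / 7.2% | 0.14 / 0.17 | 1.5% / 3.0% |
| 2 / 0.5 | none | 0.80 / 0.80 | 24.5% / 27.8% | 0.06 / 0.06 | 0.5% / 5.5% |
| 2 / 0.5 | 15% / 20% | 0.75 / 0.83 | 17.2% / 21.2% | 0.14 / 0.17 | 1.8% / 7.0% |
| 0.5 / 0.5 | none | 0.31 / 0.32 | 23.0% / 22.3% | 0.06 / 0.06 | 3.3% / 3.5% |
| 0.5 / 0.5 | 15% / 20% | 0.38 / 0.41 | 24.0% / 19.3% | 0.14 / 0.16 | 9.0% / 7.2% |

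Mean 95% half-widths were 1.32–1.40 points for the mixed model as listed against 1.55–1.76 for ANCOVA. With the interaction they were 1.53–1.71 against 1.55–1.77.

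The 2 / 0.5 rows show Step 2 at work. With no missed visits, ANCOVA averaged −2.00 at T1 and −0.42 at T2, while the mixed model as listed gave −1.21 at both, close to the midpoint −(2 + 0.5)/2 = −1.25.

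**Step 4: effect on Cohen's d.** The denominator is the pooled baseline SD under either model, so only the numerator moves. At the assumed SD of 3.5, a gap of 0.31–0.83 points is 0.31/3.5 = 0.09 to 0.83/3.5 = 0.24 in d. With the interaction it is 0.06/3.5 = 0.02 to 0.17/3.5 = 0.05.

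**Precision of these figures.** With 400 runs, the standard error of a share near 25% is √(0.25×0.75/400) = 2.2 percentage points, and near 5% it is √(0.05×0.95/400) = 1.1. The mixed-model intervals used the normal quantile and the ANCOVA intervals the t quantile. With no missed visits that is 1.988/1.960 = 1.014, so a width difference of about 1% reflects the quantile and not the model.

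**The case against.** The strongest reply is that only one analysis is meant. The first paragraph would state the aim (baseline-adjusted differences with intervals and no testing), and "Analysis will be conducted using a linear mixed model with a random effect for individual" would state how it is done. A mixed model over two visits with baseline as covariate is a repeated-measures form of ANCOVA, and the ANCOVA sentence gives no time point of its own. This reading is possible but strained: site appears in only one description, and the interval instruction is given twice. Even if it is right, the two descriptions conflict and need reconciling.

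A second reply is that ranking analyses, and spelling out every model term, can be left to a SAP that is not shown. That would answer a mere silence. Here the article states two models, and it lists fixed effects that do not fit the contrasts it promises. The interaction may well be intended, but the text does not include it.

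A third reply concerns size. Once the interaction is added the models nearly agree, so the larger disagreement comes mainly from the missing term and not from having two models. That stands.

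Several stronger readings are tempting, and the document does not support them:

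- A reader might infer that the ANCOVA breaks the statement "Analyses will be based on the intention-to-treat approach". The ANCOVA sentence does not restrict the analysis to completers and says nothing on handling missing values. The mixed model too would omit a patient with no follow-up score.
- A reader might measure the cost of the ANCOVA by how much missing visits widen its interval. That compares the ANCOVA with its own full-data version, not with the mixed model under the same missingness.
- A reader might infer that the SD for the future sample size depends on the model. Objectives {7} speaks only of the standard deviation of outcomes, and d uses the baseline SD.
- A reader might treat the MCID check as a pass/fail rule or suspect selective reporting. It is one of four considerations, and nothing in the text suggests that results would be withheld.

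**Conclusion.** The point holds at moderate weight. As written, section {20a} gives two sources for the same intervals and names neither for Cohen's d or the MCID check. That rests on the text alone. So does the finding that the mixed model as listed yields a single contrast for both visits and leaves out service type.

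The size rests on assumptions: SD 3.5, the correlations, visits missed at random, and an ANCOVA run at each visit, which is an inference. On these, the MCID answer differs between models in about 4–28% of runs with the mixed model as listed and about 0.5–9% with the interaction. Only the HPSVQ threshold of 2 points was simulated, not the PSYRATS threshold of 3, and the effect of omitting service type was not quantified.

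This is a feasibility trial without hypothesis testing, so no error rate is at stake and the trial's validity is not in question. What is affected is the clarity of one input to the choice of the future primary outcome, and of the effect sizes reported.

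**What to change.** In section {20a}:

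1. Name the linear mixed model as the single source of the reported between-group estimates, their 95% and 75% intervals, the numerator of Cohen's d, and the 95% interval used in the MCID consideration.
2. Add a group-by-time term, so that contrasts at 16 and 28 weeks can differ.
3. Enter both stratification factors, site and type of service, alongside baseline score.
4. Delete the ANCOVA sentence, or label it a sensitivity analysis that supplies neither d nor the MCID check, and state the visit or visits to which it applies.

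The cost is a few lines of protocol or SAP wording. No extra data are needed, and there is less analysis to run if the ANCOVA is deleted.

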#### Supportive Counselling (SC)

The SC intervention will follow the therapy protocol that was used by APs in the full RCT of AVATAR Therapy for distressing voices [29]. It will be delivered over the same number and duration of sessions as GiVE, with the aim of matching the duration of total therapist contact time across both arms. SC will offer a supportive and non-judgemental space for the discussion of topics and issues determined by the participant. The SC therapy protocol contains specific guidance for the AP on how to respond to participant disclosure of distressing voices in a manner that does not provide specific intervention strategies.

The intervention will involve eight sessions over a maximum of 16 weeks. Each session will last for up to 1 h, and sessions will be held weekly where possible (16 weeks are given for the eight sessions to allow for periods of absence, illness, holidays, etc.). Sessions may be delivered in NHS clinics, participants’ own homes and other community locations as preferred and appropriate. Participants in the SC arm will continue to receive their usual treatment throughout their participation in the study.

The same APs will deliver GiVE and SC in order to minimise the influence of therapist effects; for example, differing levels of therapist competence. They will receive a 5-day training in GiVE and SC (one introductory day, 2 days on GiVE and 2 days on SC), delivered by experienced clinical psychologists and an experienced counselling psychologist, respectively. Weekly clinical supervision will be provided by these clinical/counselling psychologists.

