### Sample size {14}

Following recommendations [32] for designing feasibility trials that aim to detect a small-medium standardised effect size (where the definitive trial will be designed with 90% power and two-sided 5% significance), this study aims to recruit 90 patients [33, 34]. Participants will be in contact with Community Secondary Care Adult Mental Health Services or Early Intervention in Psychosis Services at the time of consent, across two sites in the UK: (1) Sussex Partnership NHS Foundation Trust (suburban and rural); and (2) Pennine Care NHS Foundation Trust (suburban and urban).

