## Assignment of interventions: allocation

### Sequence generation {16a} and concealment mechanism {16b}

Participants will be randomly allocated using the Sealed Envelope online service https://www.sealedenvelope.com/. The trial statistician will set up and test the randomisation procedure incorporating stratification by site (Sussex or Pennine) and type of service (Community Mental Health Team or Early Intervention in Psychosis) using random block lengths and 1:1:1 allocation. Participants will be randomly allocated to receive either the study intervention and treatment as usual (GiVE) or the control intervention and treatment as usual (SC) or treatment as usual alone (TAU).

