## Oversight and monitoring

### Composition of the Trial Steering Committee (TSC) {5d}

Medical Research Council Guidelines on Good Clinical Practice in Clinical Trials [55] informed the constitution of the TSC, which includes an independent chair, independent experts and lay members.

The scientific integrity of the trial will be overseen by the TSC. The TSC will also serve the functions of a Data Monitoring and Ethics Committee (DMEC), as a combined TSC and DMEC is appropriate within the size and scope of the present feasibility trial, including oversight of the safety and data integrity of the trial.

A separate LEAP will provide Patient and Public Involvement (PPI) oversight of the trial. The LEAP will consult at regular intervals throughout the trial (approximately six meetings in total) and will advise on issues relating to design, delivery, interpretation of findings, dissemination and preparation for a future definitive RCT. Prior to the submission of the grant application for the current study, the LEAP reviewed the differences between the training and role of clinical psychologists (who delivered GiVE in our initial pilot RCT) and APs (who will deliver GiVE in the current study) and emphasised the need for APs to have experience of working with people with psychosis. This became an essential criterion for appointment to the AP post.

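### The intervals for GiVE vs TAU and SC vs TAU ignore clustering by assistant psychologist and are too narrow if outcomes vary between assistant psychologists

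*Protocol article*

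**What the plan says.** **Model.** Under Statistical methods for primary and secondary outcomes {20a}, the article plans a baseline-adjusted ANCOVA and then a mixed model: "Analysis will be conducted using a linear mixed model with a random effect for individual with fixed effects for treatment group". Time is the other fixed effect, and baseline score and site are the covariates. Intervals at 95% and 75% are planned for GiVE vs TAU, GiVE vs SC and TAU vs SC. Hypothesis tests are ruled out. For the two candidate primary outcomes, one consideration is whether the MCID (3 points on PSYRATS Distress, 2 points on HPSVQ Negative Impact) lies inside the 95% interval.

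**Delivery.** The Supportive Counselling (SC) section states: "The same APs will deliver GiVE and SC in order to minimise the influence of therapist effects", and gives as its illustration "for example, differing levels of therapist competence". The Treatment-as-usual section assigns TAU to the usual care team, so no study AP is involved in that arm.

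**Numbers.** The Sample size {14} section says "this study aims to recruit 90 patients", and the allocation section specifies "using random block lengths and 1:1:1 allocation". No section gives the number of APs or a therapist ICC.

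**The concern.** The article itself expects outcomes to depend on who delivers the therapy. Using the same APs in both therapy arms is a sound way to balance that dependence between GiVE and SC. It does nothing for a comparison with TAU, where there is no AP. Those two contrasts are partially nested: one arm is clustered by therapist and the other is not.

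The stated model treats every therapy participant as independent of every other. It therefore leaves the covariance among participants of the same AP out of the standard error of a therapy arm's mean. The participant random effect handles the repeated measures at 16 and 28 weeks, not the sharing of a therapist. The site covariate does not repair this either, because a site term shifts all three arms alike while an AP effect acts only in the two therapy arms.

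With no hypothesis tests, the intervals are the trial's main statement of uncertainty about the between-group differences. An interval that is too narrow claims more precision against TAU than the data carry, and it can exclude the MCID when an honest interval would contain it.

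**Working it through.** **The plan's own figure.** 90 participants at 1:1:1 give 90 / 3 = 30 per arm. The 90 comes from a cited rule for "designing feasibility trials that aim to detect a small-medium standardised effect size". The power and significance level given with it (90%, two-sided 5%) belong to the later definitive trial. The rule's per-arm number is not in the article, so the 90 cannot be rebuilt. It is not in dispute, and only the 30 per arm is used below.

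**Inputs**
- n = 30 per arm (from the article).
- k = number of APs, each seeing participants in both therapies. Not stated; assumed 2 to 6 over the two sites.
- ICC = share of the outcome variance in a therapy arm that lies between APs. Not stated; assumed 0.01 to 0.10.
- m = 30/k participants per AP within one therapy arm (equal caseloads assumed).
- Outcome variance set to 1 in each arm.

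**Formulas** (the same for SC vs TAU as for GiVE vs TAU)
- Design effect in a therapy arm: DE = 1 + (m − 1) × ICC.
- True variance of therapy minus TAU: DE/30 + 1/30. Naive variance: 2/30.
- SE ratio, true/naive: R = √((DE + 1)/2).
- Coverage of the naive interval: 2Φ(z/R) − 1, with z = 1.96 for 95% and 1.15 for 75%.

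**Worked cell**, k = 4 and ICC 0.05: m = 7.5; DE = 1 + 6.5 × 0.05 = 1.325; R = √(2.325/2) = 1.078; coverage of the 95% interval = 2Φ(1.96/1.078) − 1 = 93.1%.

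**SE ratio R**

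| APs | ICC 0.01 | 0.02 | 0.05 | 0.10 |
|---|---|---|---|---|
| 2 | 1.034 | 1.068 | 1.162 | 1.304 |
| 3 | 1.022 | 1.044 | 1.107 | 1.204 |
| 4 | 1.016 | 1.032 | 1.078 | 1.151 |
| 6 | 1.010 | 1.020 | 1.049 | 1.095 |

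**Actual coverage (%) of the nominal 95% / 75% intervals**

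| APs | ICC 0.01 | 0.02 | 0.05 | 0.10 |
|---|---|---|---|---|
| 2 | 94.2 / 73.4 | 93.4 / 71.9 | 90.8 / 67.8 | 86.7 / 62.2 |
| 3 | 94.5 / 74.0 | 94.0 / 72.9 | 92.3 / 70.1 | 89.6 / 66.1 |
| 4 | 94.6 / 74.2 | 94.2 / 73.5 | 93.1 / 71.4 | 91.1 / 68.2 |
| 6 | 94.8 / 74.5 | 94.5 / 74.1 | 93.8 / 72.7 | 92.6 / 70.6 |

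Over ICC 0.02 to 0.10, R runs from 1.020 to 1.304. The true SE is thus 2% to 30% larger than the naive SE. Put the other way, the naive SE is too small by 1 − 1/1.020 = 2% up to 1 − 1/1.304 = 23%.

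**Simulation.** A three-arm ANCOVA at one time point was simulated with baseline and site as covariates and APs nested in site and shared by GiVE and SC (6,000 runs per cell).
- GiVE vs TAU, ICC 0.05: coverage 90.2% / 66.2% with 2 APs and 92.0% / 70.9% with 4. At ICC 0 it was about nominal. The 2-AP case has one AP per site, so adjusting for site does not remove the problem even there.
- GiVE vs SC, AP effect common to both therapies: coverage of the 95% interval 95.2% to 96.0%.
- GiVE vs SC, half of the AP variance specific to one therapy (2 APs, ICC 0.05): 90.4% / 67.2%.

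**The case against.** **It could be left to the analysis plan.** The analysis plan is not shown, and sensitivity analyses for therapist clustering are often placed there. This would settle the matter if the article were silent on the model. It is not: it names the random effect and the covariates, and the structure it names is wrong for two of the three contrasts.

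**The stakes are modest.** This stands. There is no hypothesis testing, and the aims concern acceptability, retention, AP adherence and an SD. The MCID check is one of four considerations, beside missing data, popularity in the literature and the process evaluation. Both candidate outcomes come from the same participants and APs, so both sets of intervals are affected; nothing shows that the choice between them would change.

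**The size is assumed.** This also stands. The article refers to "This became an essential criterion for appointment to the AP post" but never says how many posts there are. Common training, detailed protocols and weekly supervision should hold the ICC down, though they do not make it zero. With 4 to 6 APs and ICC 0.02 to 0.05, coverage is 93.1% to 94.5%.

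**Intervals conditional on these particular APs are a legitimate target.** They are, but the article does not say that this is what it intends, and its Objectives concern briefly trained APs as a workforce.

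**Two stronger readings are tempting.** A reader might infer that the definitive trial will be undersized. The article says only that the SD will feed a sample size calculation; it nowhere says that a therapist design effect will be left out. A reader might also infer that GiVE vs SC is compromised. Under an AP effect common to both therapies it keeps its coverage. It falls short only if AP effects differ by therapy, which the article does not assert.

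**Conclusion.** The point holds for GiVE vs TAU and SC vs TAU, in both the ANCOVA and the mixed model. The direction follows from the article's own design: with a positive therapist ICC and more than one participant per AP, the stated 95% and 75% intervals are too narrow. The size rests on assumptions about the number of APs, the ICC and equal caseloads. Over 2 to 6 APs and ICC 0.02 to 0.10, the 95% interval covers between 94.5% and 86.7%, and the 75% interval between 74.1% and 62.2%. The lower ends belong to one corner only (2 APs, ICC 0.10) and should not be quoted as the expected loss. This is a moderate fault in how precision is reported and in the MCID check. It does not threaten the feasibility aims, and it is worth correcting because the correction is cheap.

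**What to change.** Keep the stated model and add the following for the two therapy vs TAU contrasts only:

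1. A partially nested sensitivity analysis with a random effect for AP in the GiVE and SC arms and none in TAU.
2. If there are too few APs to estimate that variance, which is likely at the low end of the assumed range, report instead the 95% and 75% intervals with half-widths multiplied by √((DE + 1)/2) under assumed ICCs of 0.01, 0.05 and 0.10, using the actual number of APs. With 2 APs the multipliers would be 1.034, 1.162 and 1.304; with 6 APs, 1.010, 1.049 and 1.095.
3. In the MCID check, show these intervals beside the unadjusted ones.

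The number of APs should be stated. No change is needed for GiVE vs SC. An AP fixed factor there is optional, requires a separate two-arm fit because TAU has no AP, and would duplicate the site covariate if each site has one AP.

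The cost is a short addition to the analysis plan, one extra table and slightly wider intervals. No new data collection should be needed: APs are notified of their own participants (Implementation {16c}) and complete a checklist after each session (Strategies to improve adherence to interventions {11c}).

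### Type of service is a randomisation stratum but is missing from the stated covariates, so the intervals are conservative if it predicts outcome

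*Protocol article*

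**What the plan says.** Sequence generation {16a} sets up randomisation with "stratification by site (Sussex or Pennine) and type of service (Community Mental Health Team or Early Intervention in Psychosis" as the two factors, "using random block lengths and 1:1:1 allocation". That gives 2 × 2 = 4 strata.

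Statistical methods {20a} then describes the between-group analysis twice. The first paragraph gives confidence intervals for mean differences "after adjustment for the baseline scores using analysis of covariance (ANCOVA", with no other covariate named. The second paragraph describes a linear mixed model with a random effect for individual and fixed effects for group and time, and says "baseline score and site will be entered as covariates". Both paragraphs list the same three pairwise comparisons and the same two interval levels, and the second says that "95 and 75% confidence intervals [25] for between-group mean differences will be created for all estimates of unstandardised effect size".

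The same section says "There will be no hypothesis testing". For the two candidate primary outcomes it asks "Whether the minimal clinically important difference (MCID) is contained within the 95% confidence intervals". The MCIDs are 3 points on the PSYRATS distress scale and 2 points on the HPSVQ negative impact scale.

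Type of service appears in no analysis section, and no reason is given for leaving it out.

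**The concern.** Blocking within strata balances each stratification factor across the arms. The between-service part of the outcome variance is therefore largely removed from the true sampling variance of a between-arm difference. A model without the factor does not know this. It leaves that variance in the residual, and its standard error overstates the real uncertainty.

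The mixed model recognises one stratification factor and leaves out the other. The ANCOVA, read literally, recognises neither. If service type is related to outcome, both sets of intervals are wider than the design warrants. The intervals are the main between-group result of this study, and an over-wide 95% interval contains the MCID more readily. That bears, in a small way, on the choice of primary outcome for the definitive trial.

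**Working it through.** **Inputs from the protocol.** Planned total 90, allocated 1:1:1 (Sample size {14}, Sequence generation {16a}). Two binary stratification factors with random block lengths ({16a}). Covariates: baseline score for the ANCOVA; baseline score and site for the mixed model ({20a}). Interval levels 95% and 75% ({20a}).

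**Assumed, because the protocol does not give them.** Baseline–outcome correlation 0.5; blocks of 3 or 6; half of participants at each site; 30% or 50% in Early Intervention; site effects of 0 to 0.3 SD; service effects of 0 to 0.8 SD, independent of baseline score. SD means the outcome SD within a stratum.

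The plan states no figure on this point, so there is none to reproduce.

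**Step 1: formula.** Let the service effect be b, the share in one service p, and the residual variance after baseline adjustment 1 − 0.5² = 0.75. Leaving service out adds p(1 − p)b² to the residual variance, so

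width ratio ≈ √[(0.75 + p(1 − p)b²) / 0.75].

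- b = 0: ratio 1, no widening.
- b = 0.2, p = 0.3: √(0.7584/0.75) = 1.006
- b = 0.5, p = 0.3: √(0.8025/0.75) = 1.034
- b = 0.5, p = 0.5: √(0.8125/0.75) = 1.041
- b = 0.8, p = 0.5: √(0.91/0.75) = 1.102

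Equivalently, if service type explains a share R² of the residual variance, the widening is 1/√(1 − R²) − 1. This is 0%, 2.6%, 5.4% and 8.5% for R² of 0, 0.05, 0.10 and 0.15.

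**Step 2: simulation.** 6,000 trials of 90 participants per scenario, with permuted blocks within site × service, analysed by least squares at one time point. Each cell gives ANCOVA (baseline only) / baseline + site / baseline + site + service, for one pairwise contrast with no true difference.

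| Site effect, service effect, Early Intervention share | Mean 95% width (SD) | 95% coverage (%) | 75% coverage (%) |
|---|---|---|---|
| 0, 0, 30% | 0.892 / 0.893 / 0.893 | 94.8 / 94.8 / 94.9 | 75.2 / 75.2 / 75.0 |
| 0.2, 0.2, 30% | 0.905 / 0.899 / 0.895 | 95.4 / 95.3 / 95.3 | 76.1 / 75.6 / 75.5 |
| 0.3, 0.5, 30% | 0.937 / 0.924 / 0.893 | 96.0 / 95.7 / 95.2 | 77.1 / 76.4 / 74.7 |
| 0.3, 0.5, 50% | 0.944 / 0.932 / 0.894 | 96.2 / 96.0 / 95.1 | 77.7 / 77.3 / 74.9 |
| 0.3, 0.8, 50% | 0.999 / 0.987 / 0.895 | 97.2 / 97.1 / 95.4 | 80.9 / 80.4 / 75.9 |

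The Monte Carlo standard error of coverage is √(0.95 × 0.05/6000) ≈ 0.3 percentage points at 95% and √(0.75 × 0.25/6000) ≈ 0.6 points at 75%.

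**Step 3: width against the fully adjusted model.**

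- Baseline + site: 0.8992/0.8949 = 1.005 at 0.2 SD. At 0.5 SD, 0.9240/0.8931 = 1.035 (30% share) and 0.9316/0.8943 = 1.042 (50% share). At 0.8 SD, 0.9873/0.8945 = 1.104. These agree with Step 1.
- ANCOVA as literally written: 0.9046/0.8949 = 1.011, 0.9441/0.8943 = 1.056 (50% share) and 0.9993/0.8945 = 1.117. Part of this comes from the missing site term.

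**Step 4: where the fault lies.** In the 0.8 SD scenario the estimate's actual standard error over the simulated trials was 0.2225, 0.2224 and 0.2212 for the three models, which is practically the same. The baseline + site model reports about 0.9873/(2 × 1.988) = 0.248. So the estimate already has the benefit of stratification, and only the reported standard error misses it.

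**Step 5: cost of adjusting.** At one time point, residual degrees of freedom fall from 90 − 5 = 85 to 84. With no service or site effect, the mean width is 0.893 either way.

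**The case against.** The strongest case against is that this hardly matters. The study is estimation only, and its stated aims are acceptability, recruitment and retention, adherence, and an estimate of the outcome SD. Any error is conservative and may be nil. The MCID check is one of four considerations, alongside missing data, popularity in the literature and process-evaluation information. Explaining 5%, 10% or 15% of residual variance with an even service split needs a difference of 2√[R²/(1 − R²)] = 0.46, 0.67 or 0.84 residual SD, and nothing in the protocol shows effects of that size. All of this stands, and it limits the weight of the point.

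It can also be said that the ANCOVA sentence is only a loose description of the mixed model that follows, since both give the same contrasts and intervals. That reading is possible. On it, site is adjusted for and only type of service is missing.

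That a journal article condenses the full plan does not dispose of the point. The article does not leave the covariates open. It lists them, and the list contains one stratification factor and not the other.

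A reader might infer more than the protocol supports:

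- **Bias or under-coverage.** Neither follows. Estimates are unbiased, and coverage is at or above nominal.
- **That the gain from stratification is lost.** Step 4 shows that it stays in the estimate.
- **That an inflated residual SD will feed the definitive sample size.** Objectives {7} speaks only of the standard deviation of outcomes, and {20a} standardises effects by the baseline pooled SD. Neither a raw SD by arm nor the baseline SD changes when a covariate is added to the model.
- **A particular clinical reason for stratifying on service type.** None is stated.

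**Conclusion.** The mismatch is certain from the text: two stratification factors, one in the mixed model, and none in the ANCOVA if that sentence is taken literally. The consequence is conditional and modest. If service type predicts outcome beyond baseline score and site, the model-based standard errors and both sets of intervals are conservative. For the mixed model's covariates, the widening is about 0%, 0.5%, 4% and 10% at assumed service effects of 0, 0.2, 0.5 and 0.8 SD. The 95% interval then covers up to about 97%, and the 75% interval up to about 80%.

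These sizes rest on the assumed correlation, service shares and block sizes, and on a single-time-point model rather than the full mixed model. The direction does not depend on the particular values chosen. The practical effect is confined to somewhat over-wide intervals and a slightly easier MCID check. This is a free improvement to the plan rather than a threat to the study's conclusions.

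**What to change.** In Statistical methods {20a}, list baseline score, site and type of service as covariates in the mixed model. If the ANCOVA is a separate analysis, give it the same three covariates. If it is not, say so, or delete the sentence and let the mixed model stand as the single specification. If type of service is left out on purpose, state the reason.

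The cost is a change of wording and one degree of freedom. No new data are needed, because service type must be known for every participant in order to randomise within strata.
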